### Preintervention Procedure

The preintervention appointment will be conducted by a CDE at the study hospital. The CDE will ensure the participant consent form has been completed before commencing the preintervention appointment. The CDE will discuss the study procedure to ensure the participant understands what is required during all phases of the intervention. The CDE will record the participants’ weight (kg) and height (cm) using a seca 763 electronic measuring station. This information will be recorded on a participant data collection form which will be used pre- and postintervention. An HbA_1c_ test will be conducted using a DCA Vantage Analyzer (Siemens Healthineers). Participants will complete the online Australian diabetes-specific QoL questionnaire using a hospital computer. The CDE will provide each participant with a Dexcom G6 CGMS kit. The kit includes a transmitter, sensors, and a sensor applicator, as provided by Dexcom. Novice CGMS participants will be taught how to use the device. During this appointment, the participant will apply the CGM sensor to their abdominal wall, attach the transmitter, and establish a connection between the transmitter and their own compatible smart device to enable recording and displaying of their glucose levels. Participants glucose levels will then record and display glucose level via the Dexcom G6 application, which the participant will install onto their compatible smart device. The Dexcom G6 CGMS kit will be retained by the participant at the completion of the study. Participants will not use their own personal glucose monitor during the study to test blood glucose levels. However, the participant will use it weekly to test blood ketones. The participant will also be required to use their own blood ketone strips for this test.

Participants will continue with their usual, daily routine; however, they will commence recording food and fluid consumption in a food diary. Participants will be required to complete the daily food diary 1 week prior to commencing the intervention and for the 12 weeks of the intervention. The participant will email this information to the diabetes dietitian weekly to ensure these records are being maintained, as the information will be used in the final data analysis stage. Participants’ individualized meal plans will be emailed to each participant the day prior to commencing the intervention. Each participant will also be provided with digital kitchen scales and measuring cups and spoons to assist with weighing and measuring foods and fluids to ensure accuracy of quantities consumed. These instruments have been supplied by the GCHHS Study, Education and Research Trust Account (SERTA).

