The preintervention period will begin 1 week prior to commencing the intervention procedure. Participants will attend the study hospital for approximately 3 hours to do the following: complete the study consent form (hard copy), if not already completed; discuss the intervention process ensuring they have a clear understanding of what is required during all phases of the intervention; receive an information kit containing the study procedure, the research team (endocrinologist [PD], credentialed diabetes educator [CDE; DI], and diabetes dietitian [JP]) and Gold Coast Hospital Emergency Department contact details, a food diary, a sick day management plan, and support services (in case any psychological distress is experienced during the study); complete the online Australian diabetes-specific QoL questionnaire; have weight (kg), height (cm), and glycated hemoglobin (HbA_1c_) recorded; receive continuous glucose monitoring system (CGMS) education and supply of CGMS equipment; apply the CGM sensor to their abdominal wall, attach the transmitter, and establish a connection between the transmitter and their own compatible smart device in order to enable recording and displaying of their glucose levels; and receive instruction on how to continue with their usual, daily routine, and be asked to commence recording what they eat and drink via a food diary. The day prior to commencing the intervention, participants will receive their individualized meal plans by email.

The intervention procedure will take place in the participants own environment and last 12 weeks. Participants will be expected to perform the following during the intervention period: follow the low carbohydrate dietary plan (dietary composition: 20% carbohydrate [<100 g], protein 25%, and fat 55%) as prescribed by a diabetes dietitian, complete a daily food diary, test blood ketone levels weekly (at fasting), participate in a weekly endocrinologist appointment to discuss blood glucose levels and insulin adjustments by telephone, attend the diabetes dietitian appointment by telephone to discuss any concerns with the dietary plan, contact DI if having problems with the CGMS, and change the CGM sensor every 10 days.

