### Participant Eligibility Criteria

#### Inclusion Criteria

Study participants for each phase will self-identify against the following eligibility criteria: aged ≥18 years, living with T1DM, and T1DM diagnosis for ≥1 year. Study phase 3 includes 5 additional eligibility criteria that participants must meet: (1) use of multiple daily injections for insulin administration, (2) experience of at least one hypoglycemic episode since diagnosis, (3) knowledge of hypoglycemic management, (4) ability to test for blood ketones, and (5) knowledge of blood ketone management. 

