### Intervention Procedure

All participants will follow a prescribed meal plan to meet their estimated energy needs as per the Schofield formula [64]. Meal plan macronutrient distribution will be 20% carbohydrate, 25% protein, and 55% fat based on the Australian book, *The CSIRO Low Carb Diet* [65]. The meal plan contains no more than 100 g per day of dietary carbohydrate, making this intervention a low carbohydrate dietary regimen according to Feinman et al’s [16] 2015 definition. Alcohol influences blood glucose levels, food and fluid choices, and quantities consumed [66]. For this reason, participants will be strongly advised to abstain from alcohol consumption during the 12-week intervention. Weekly telephone follow-up will be conducted by JP to discuss any concerns or questions participants may have. Follow-up by telephone has been shown to be an effective method to monitor medical nutrition therapy [67,68]. Weekly telephone appointments will also be conducted by the research teams’ endocrinologist (PD) to discuss blood glucose level management and adjust insulin doses as needed.

Any hypoglycemia treatment will be recorded in the food diary and will detail when, what, and how much carbohydrate was used to treat the hypoglycemic event. If any hypoglycemic events occur, PD will discuss this with the participant during the weekly telephone appointment and advice will be provided to avoid future occurrences. Participants will check blood ketones once a week on the morning after an overnight fast to avoid diabetic ketoacidosis. If blood ketones are present (>0.6 mmol/l), participants will follow a “sick day” management plan, and, if unsure what to do, will contact PD for advice. Participants will be encouraged to follow their usual exercise habits, as no exercise advice will be given [69]. This study is unique, and if a participant feels they are unable to complete the 12-week intervention, they may withdraw at any time.

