### Potential Adverse Events

Potential adverse events may include hypoglycemia, hyperglycemia, blood ketones, and diabetic ketoacidosis episodes. Any adverse events will be discussed by PD and the participant, and a plan will be put in place to prevent any future occurrences. However, adverse events are not expected to occur due to the safety alerts thresholds that will be set up on the CGM as recommended by the CGM use guidelines [71].

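### The ban on own-meter glucose testing has no exception for CGM failure, leaving insulin-injecting participants without a permitted home reading when the CGM is down

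*Protocol article*

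**What the plan says.** All statements are in the protocol article and concern phase 3.

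- **The rule.** Preintervention Procedure: "Participants will not use their own personal glucose monitor during the study to test blood glucose levels". The sentence that follows restores one use of the meter: "However, the participant will use it weekly to test blood ketones".
- **The equipment.** Same section: "The kit includes a transmitter, sensors, and a sensor applicator, as provided by Dexcom". Readings are shown on the participant's own smart device. No study blood glucose meter is listed.
- **Interruptions foreseen.** Study Outline, Study Phase 3, tells participants to contact the diabetes educator if "having problems with the CGMS, and change the CGM sensor every 10 days".
- **The population.** Inclusion Criteria requires "use of multiple daily injections for insulin administration".
- **Glucose-dependent decisions.** Intervention Procedure: "Any hypoglycemia treatment will be recorded in the food diary". The weekly endocrinologist calls are "to discuss blood glucose level management and adjust insulin doses as needed".
- **The safety argument.** Potential Adverse Events says that "adverse events are not expected to occur due to the safety alerts thresholds that will be set up on the CGM".

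**The concern.** Participants inject insulin several times a day and move to a diet with no more than 100 g of carbohydrate daily, with doses adjusted along the way. Hypoglycemia, hyperglycemia and ketoacidosis are all named as possible events. The plan makes the CGM the sole source of home glucose values and, through its alerts, the sole stated reason for expecting no adverse events. It then rules out the obvious fallback, the participant's own meter, without saying what to do when the CGM is silent.

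During an outage the glucose value and the alerts disappear together. A participant who follows the instruction exactly would dose insulin or treat symptoms without a reading. One who sensibly uses a fingerstick would be departing from the written rule. What is at stake is participant safety and clear instructions, not the statistical analysis.

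**Working it through.** The plan states no figure to reproduce here. The check is whether any part of the article softens the rule or supplies another reading, followed by simple arithmetic for scale.

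**Search for an exception or a back-up**

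| Section | What it offers | Does it give a glucose reading during an outage? |
|---|---|---|
| Preintervention Procedure (rule) | No own-meter glucose testing during the study; weekly ketones remain | No |
| Preintervention Procedure (kit) | Transmitter, sensors, applicator | No; no meter or glucose strips listed |
| Study Outline, Study Phase 3 | Contact with the educator for CGM problems; information kit with sick day plan and emergency department details | Not stated; a contact is not a measurement |
| Intervention Procedure | Weekly calls; sick day plan followed when ketones exceed 0.6 mmol/l | Not stated; the trigger is ketones, not loss of CGM signal |
| Potential Adverse Events | CGM alerts; discussion with the endocrinologist after an event | No; alerts stop with the CGM |
| Inclusion Criteria | Prior hypoglycemia, knowledge of its management, ability to test ketones | No |
| Data Collection, Phase 3 | Lists CGM use for 12 weeks among the requirements | No |

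No section permits a fingerstick when the CGM gives no value.

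**Points at which the CGM can fail.** A home reading needs the sensor, the transmitter, the connection and the participant's own device all to work. The loss of any one removes both the reading and the alert.

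**Scale**

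- Time under the rule: 1 preintervention week + 12 intervention weeks = 7 + 84 = 91 days per participant, for up to 23 participants (Sample Size, Study Phase 3).
- Planned sensor changes: 91 / 10 = 9.1, so about 9 per participant, before any failure.
- Stated meter use: about 12 ketone tests (one a week for 12 weeks) and 0 glucose tests.
- Hours under the rule: 91 × 24 = 2184.
- Illustration only: if 1% of that time had no reading, 0.01 × 2184 = 21.8 hours; if 5%, 0.05 × 2184 = 109.2 hours. The 1% to 5% range is an assumption, as the documents give no frequency or length of outages.

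**Reach into the outcomes.** HbA1c is measured at the hospital on a separate analyzer before and after the intervention, so the HbA1c outcome and the sample size and power based on it do not depend on home readings.

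**The case against.** The strongest reply is that the sentence names the routine method: it sits in a paragraph on issuing and connecting the CGM, and the authors probably meant that CGM replaces everyday self-monitoring. The word *only* does not appear, so a ban during device failure is an inference. The article is also a condensed account. Instructions for device failure would naturally sit in the CGM education, the information kit or the sick day plan, none of which is shown. Participants keep their meter, know how to manage hypoglycemia, and have an educator to call who might well advise using it.

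Part of this stands. The intent was probably benign, the unseen materials may contain a contingency, and a participant dosing without a value is the worst case, not the expected one. The hours quoted above rest on no evidence from the documents. It is also true that testing when symptoms and reading disagree goes slightly beyond the case of a missing reading.

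It does not remove the point. This is not a detail the article leaves out but a rule it states, and the contrast with the next sentence makes weekly ketones the one use that survives. An exception held elsewhere would contradict the published instruction. The safeguards listed provide advice or knowledge, not a glucose value.

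**Conclusion.** The concern holds. As written, the rule leaves phase 3 participants without a permitted home glucose reading whenever the CGM is not working, for 91 days in up to 23 people, and at those moments the alerts on which the safety statement relies are missing too.

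The conclusion rests on reading the two adjacent sentences together as a ban with one carve-out, and on the absence of any exception in the article. It does not rest on the assumed outage range: how many hours are affected cannot be derived from the documents. The consequence is confined to safety and conduct. No outcome, analysis, sample size or power figure changes. The sentence should be corrected because the gap is foreseeable and the correction costs very little.

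**What to change.** Qualify the sentence under Preintervention Procedure and make the participant instructions match, along these lines:

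> CGM replaces routine self-monitoring of blood glucose. Fingerstick testing with the participant's own meter is allowed whenever the CGM gives no reading (sensor change, sensor failure or lost connection) or does not match symptoms. These readings are recorded for the weekly endocrinologist call.

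The symptom-mismatch clause is a small extension that fits naturally in the same sentence.

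**Cost.** One sentence and a matching line in the instructions. Participants already hold the meter. They will need glucose strips as well as ketone strips, and a few non-CGM readings will sit beside the CGM record. No visit, outcome or analysis changes.

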### Intervention Procedure

All participants will follow a prescribed meal plan to meet their estimated energy needs as per the Schofield formula [64]. Meal plan macronutrient distribution will be 20% carbohydrate, 25% protein, and 55% fat based on the Australian book, *The CSIRO Low Carb Diet* [65]. The meal plan contains no more than 100 g per day of dietary carbohydrate, making this intervention a low carbohydrate dietary regimen according to Feinman et al’s [16] 2015 definition. Alcohol influences blood glucose levels, food and fluid choices, and quantities consumed [66]. For this reason, participants will be strongly advised to abstain from alcohol consumption during the 12-week intervention. Weekly telephone follow-up will be conducted by JP to discuss any concerns or questions participants may have. Follow-up by telephone has been shown to be an effective method to monitor medical nutrition therapy [67,68]. Weekly telephone appointments will also be conducted by the research teams’ endocrinologist (PD) to discuss blood glucose level management and adjust insulin doses as needed.

Any hypoglycemia treatment will be recorded in the food diary and will detail when, what, and how much carbohydrate was used to treat the hypoglycemic event. If any hypoglycemic events occur, PD will discuss this with the participant during the weekly telephone appointment and advice will be provided to avoid future occurrences. Participants will check blood ketones once a week on the morning after an overnight fast to avoid diabetic ketoacidosis. If blood ketones are present (>0.6 mmol/l), participants will follow a “sick day” management plan, and, if unsure what to do, will contact PD for advice. Participants will be encouraged to follow their usual exercise habits, as no exercise advice will be given [69]. This study is unique, and if a participant feels they are unable to complete the 12-week intervention, they may withdraw at any time.

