#### Study Phase 3: The Low Carbohydrate Dietary Intervention

A sample size of 16 has been calculated with a 0.05 significance level and power of 0.8 to detect a significant clinical difference of 1.0% in HbA_1c_. A 1.0% change in HbA_1c_ will be used because dietary changes alone have shown to improve HbA_1c_ by 1.0% [60]. To complete the study, 16 participants are required. To account for a 40% attrition rate [12], 23 participants will be the maximum number recruited.

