## Discussion

This study is the first of its kind to examine the association between a low carbohydrate diet, QoL, and glycemic control. This cross-sectional study protocol aims to develop, pilot, and validate a diabetes-specific QoL questionnaire and determine if an association exists between QoL and glycemic control while using a low carbohydrate dietary intervention in Australian adults living with T1DM.

The strengths of this study are that, to our knowledge, no previous published research has evaluated a low carbohydrate diet and its influence on QoL and glycemic control in Australian adults living with T1DM. Moreover, this is the first study to develop and validate an Australian T1DM-specific QoL questionnaire Therefore, the strengths of this study are its unique approach.

The potential limitations of this study include the fact that, first, the Australian diabetes-specific QoL questionnaire is not available to those who are vision impaired, intellectually impaired, or have any other type of diabetes, such as T2DM and gestational diabetes mellitus. Future studies could develop resources to include these populations. Second, in study phases 1 and 2, questionnaire data will be self-reported and may have the potential to produce social desirability bias [73]. However, using self-reported data is the most feasible option for this pilot study in order for the sample size (N=364) and statistical validation of the questionnaire to be achieved. Third, study phase 3 has been designed as a nonrandomized intervention group pilot study that will inform the design and feasibility of a potential larger randomized control trial. Finally, in study phase 3, there is potential selection bias: individuals who are highly motivated to improve glycemic control are more likely to participate [25].

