The Australian diabetes-specific QoL questionnaire will be a useful instrument for health care professionals, including general practitioners, diabetes dietitians, and diabetes educators. This instrument will support health care practitioners to gain a better understanding of Australian T1DM adults’ QoL perception relating to physical, psychological, social, and dietary well-being. To date, studies that have investigated the influence of a very low or low carbohydrate diet and glycemic control in adults living with T1DM have not examined QoL using a validated instrument in tandem with participants undertaking the dietary regimen [12,13,19,21,23-31]. Consequently, a validated QoL instrument is needed for clinical practice and future research to identify the QoL of Australian adults with T1DM, as no validated instrument currently exists.

It is recommended that people living with T1DM follow healthy eating dietary guidelines for the general population [3]. However, this study’s dietary intervention outcomes could provide an alternative approach. Additionally, the study findings could warrant the development of a specific dietary guideline for using a low carbohydrate diet to support glycemic management and improve QoL in adults living with T1DM.

This study will generate a new validated QoL instrument which could be used in evidence-based practice and research to understand the QoL of adults with T1DM. It will also investigate the association of a low carbohydrate diet, QoL, and glycemic control in Australian adults living with T1DM. If successful, this study has the potential to have a profound impact on those living with T1DM.

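### Phase 3 names the diet alone as the exposure, but every participant also starts CGM and weekly insulin adjustment between the two HbA1c measurements, so the change belongs to the package and cannot be attributed to the diet

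*Protocol article*

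**What the plan says.** **Design.** The Discussion states that "study phase 3 has been designed as a nonrandomized intervention group pilot study", meant to inform a potential larger randomized trial. There is no unexposed group: "All participants will follow a prescribed meal plan to meet their estimated energy needs" (Intervention Procedure). HbA1c is measured at the preintervention visit and again after the intervention.

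**What else changes between the two measurements.**
- CGM: "The CDE will provide each participant with a Dexcom G6 CGMS kit" (Preintervention Procedure). Readings appear on the participant's own device, novice users are taught, and the CGM takes over from the usual meter: "Participants will not use their own personal glucose monitor during the study to test blood glucose levels". It starts one week before the diet, at the visit where baseline HbA1c is taken.
- Insulin: weekly telephone appointments with the endocrinologist "to discuss blood glucose level management and adjust insulin doses as needed" (Intervention Procedure).
- Alcohol: "participants will be strongly advised to abstain from alcohol consumption during the 12-week intervention" (Intervention Procedure).

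**What the change is linked to.** Primary outcome 3.1 (Outcomes) and the matching row of Table 4 name only the low carbohydrate diet as the independent variable for glycemic control. The planning effect rests on the statement that "dietary changes alone have shown to improve HbA_1c_ by 1.0" percent (Sample Size, Study Phase 3). The Discussion adds that "the study findings could warrant the development of a specific dietary guideline for using a low carbohydrate diet", and the abstract's Conclusions say much the same.

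**What is disclosed.** The limitations in the Discussion name the nonrandomized pilot design and possible selection of motivated volunteers. They do not mention CGM, insulin adjustment or alcohol advice.

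**The concern.** The objective, the planning effect and the foreseen conclusion all concern the diet. What is delivered is the diet plus at least two other components that could lower HbA1c by themselves, given to everyone over the same interval. If HbA1c falls, the plan as written reports this as the result for diet and glycemic control, although a fall of the same size could come wholly or partly from CGM and insulin adjustment.

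The protocol itself treats these components as active. Under Potential Adverse Events it expects CGM alert thresholds to prevent hypo- and hyperglycemia. The Introduction describes intensive insulin therapy as convincingly effective in T1DM. The Intervention Procedure says that alcohol affects glucose. At stake is a primary conclusion credited to the wrong cause and then carried into talk of a dietary guideline.

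**Working it through.** **1. What the design identifies.** Let D be the effect of the diet on HbA1c over 12 weeks and C the combined effect of CGM, insulin adjustment and alcohol advice, including any interaction with the diet. Every participant has all components, so

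expected before-after change = D + C.

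The data give one mean change and there are two unknowns. Starting CGM a week before the diet does not help, because baseline HbA1c is taken at the visit where CGM begins. C therefore falls inside the measured change. For participants who already used CGM, that part of C would be smaller.

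**2. The plan's own figure.** Sample Size gives 16 completers to detect 1.0 percentage point at a 0.05 significance level with power 0.8. No SD and no test are stated, so 16 cannot be reproduced uniquely. It fits:
- a two-sided paired t-test with SD of change about 1.33 (n = 16, power 0.80);
- a one-sided paired t-test with SD 1.5 (n = 16, power 0.82);
- a two-arm normal approximation with 16 per arm at SD 1.0, or 16 in total at SD 0.7.

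The abstract names change in HbA1c over 12 weeks as a primary outcome and there is one group, so the paired reading is used below. It is an assumption.

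**3. Illustration of false attribution.** Set D = 0, so any expected fall comes from C alone. For a two-sided paired t-test at 0.05 with n = 16, the test statistic is noncentral t with 15 degrees of freedom and noncentrality

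(C / SD) × √16 = 4C / SD.

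Examples: C = 0.2, SD = 1.33 gives 0.60; C = 0.4, SD = 1.0 gives 1.6; C = 0.6, SD = 0.8 gives 3.0. The probability of a significant result is:

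| Assumed C (percentage points) | SD 0.8 | SD 1.0 | SD 1.33 |
|---|---|---|---|
| 0 | 5% | 5% | 5% |
| 0.2 | 16% | 12% | 9% |
| 0.4 | 47% | 32% | 20% |
| 0.6 | 80% | 61% | 39% |

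Neither C nor the SD is in the documents. The table shows only that the 5% level does not protect a statement about the diet once C differs from zero. It does not estimate this trial's error rate.

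**4. Is a small diet effect plausible?** The controlled study described in the Introduction, a randomized crossover of low against high carbohydrate intake in T1DM, found no significant HbA1c improvement. That does not show D = 0, but it means an uncontrolled fall cannot safely be credited to the diet by default.

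**The case against.** **The wording is modest.** The objectives speak of an association, the Outcomes section says its direction is unclear, the guideline is only something that could be warranted, and the pilot status is disclosed. This stands in part. A reader might infer that the protocol asserts a causal diet effect, and it does not say so. But with everyone on the diet there is no contrast from which a before-after association with the diet alone could be read, and the guideline statements bypass the randomized trial that the limitations say should follow.

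**Not every component is a rival cause.** This stands. The weekly dietitian calls are how the diet is delivered and monitored. Alcohol abstinence is advised, not required. CGM alerts are presented as a safety measure and insulin adjustment accompanies the meal plan, so one may view the intervention as a supervised diet. On that view the outcome should name the supervision. CGM and insulin adjustment remain the serious competing explanations.

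**Regression to the mean.** A reader might add this as a further cause of a fall. The documents do not support it well: the eligibility criteria set no HbA1c threshold, and selection on motivation is a different bias that is already disclosed.

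**The probabilities are not the plan's.** This stands. Table 4 lists ANOVA, correlations and hierarchical regression, not a paired t-test. If those analyses relate HbA1c change to recorded intake from the food diary, a shift common to all participants would not move the slope. That would be a different question from the 1.0-point change used for the sample size, and insulin is adjusted individually as needed, so its effect need not be common to all.

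**Conclusion.** The point holds as one of attribution. In a single group receiving the diet together with CGM and weekly insulin adjustment, the HbA1c change estimates the package. Outcome 3.1, Table 4 and the guideline statements name the diet alone, and the limitations do not mention the co-interventions. This follows from the design and needs no assumed effect size.

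Its size is unknown. The range of about 9% to 80% depends on an assumed paired t-test with 16 completers, no diet effect, a co-intervention shift of 0.2 to 0.6 and an SD of change of 0.8 to 1.33. A reader might infer that a particular false-positive rate, or a particular share of an observed 1.0-point fall, has been shown to be non-dietary. The documents support neither. Nor do they show that the diet has no effect; they show only that this design cannot tell.

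**What to change.** - Restate primary outcome 3.1, the matching Table 4 row and the conclusion as change in HbA1c under a low carbohydrate diet delivered with CGM and weekly insulin adjustment.
- In the abstract's Conclusions and the Discussion, replace the guideline statements with the aim already given in the limitations: informing a larger randomized trial.
- Add CGM and insulin adjustment, and secondarily the alcohol advice, to the limitations as competing explanations.
- Record prior CGM use at entry and insulin dose during follow-up, if the full study forms do not already do so. Report both descriptively only. About 16 completers are too few for an informative split by prior CGM use, and insulin dose may itself change because of the diet, so adjusting for it would not isolate the diet.
- Label any comparison of CGM data between the run-in week and the diet weeks as exploratory. It holds CGM wear constant but not insulin adjustment or alcohol advice, and one week is a short baseline that includes learning by novice users.

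Treatment, visits and sample size stay as they are. The cost is rewording, at most two data fields, and a less favourable stated conclusion.
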